### **Methods for the randomization**

The patients will be selected from the list of diabetic patients followed in diabetes consultations of Bamako.

From this numbered list, a selection will be will randomly conducted with a number table to constitute the intervention group. We will verify that all the patients randomly selected to form this group meet the inclusion criteria of the group (see below).

The randomization list will be kept by the principal researchers of the survey.

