### **Inclusion criteria**

- Patients followed in the diabetes units of the project area and doing regular consultations
- Patients with type 2 diabetes or treated or not with insulin
- Poorly controlled diabetes with HbA1c  $\geq 8\%$
- Patients who accepted to undergo the whole process of peer education
- Patients who agreed to perform all biological measures included in the protocol
- Patients aged from 30 to 70 years old

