## Chronogram

|                            | Month 1 - 5 | Month 6       | Month 7                  | Month 8          | Month 9      | Month 10      | Month 11       | Month 12 |
|----------------------------|-------------|---------------|--------------------------|------------------|--------------|---------------|----------------|----------|
|                            | Preparation | Randomization | Pre inclusion
T-X (*) | Inclusion
T 0 | Visit
T 3 | Visite
T 6 | Visite
T 12 |          |
| Identification of patients | ✓           | ✓             |                          |                  |              |               |                |          |
| Patient Education experts  | ✓           |               |                          |                  |              |               |                |          |
| Informed Consent           |             |               | ✓                        |                  |              |               |                |          |
| Clinical examination       |             |               | ✓                        | ✓                | ✓            | ✓             | ✓              |          |
| Laboratory tests           |             |               | ✓                        | ✓                | ✓            | ✓             | ✓              |          |
| Knowledge                  |             |               | ✓                        | ✓                | ✓            | ✓             | ✓              |          |
| Data Processing            |             |               |                          |                  |              |               |                | ✓        |
| Report                     |             |               |                          |                  |              |               |                | ✓        |

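### As written, the allocation procedure does not secure a randomised comparison: only the intervention group is drawn and checked, control formation is not described, and consent follows randomisation

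*Supplement*

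**What the plan says.** Under Methods for the randomization, the starting point is an existing clinic list: "The patients will be selected from the list of diabetic patients followed in diabetes consultations of Bamako". From it a selection is "randomly conducted with a number table to constitute the intervention group". The next sentence gives the eligibility check: "We will verify that all the patients randomly selected to form this group meet the inclusion criteria of the group (see below". The section ends by leaving the randomisation list with the principal researchers. No step describes how the control group is obtained or checked.

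The Inclusion criteria contain "Poorly controlled diabetes with HbA1c" of at least 8%, and also "Patients who accepted to undergo the whole process of peer education". Under Comparison group, controls have the usual individual consultations and do not follow peer education.

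The Chronogram columns run "Preparation | Randomization | Pre inclusion T-X (*) | Inclusion T 0". The rows "Informed Consent" and "Laboratory tests" are first ticked under pre-inclusion, one column after randomisation.

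Elsewhere the protocol declares a randomised trial. The scientific abstract proposes person-level randomisation, the sample size section says patients are randomised into two groups and calls the trial open, and Ethical consideration says half the subjects are denied the programme at random.

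**The concern.** A randomised comparison needs one pool of eligible, consenting patients who are split by chance. Here chance is used to pick one group from a list that has been neither screened nor consented, and eligibility and consent follow. Patients can then leave for reasons linked to the arm they are in.

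The acceptance criterion is the clearest case. A patient drawn for education can refuse it and be dropped as ineligible, while a control has no matching offer to refuse. The patients left in the education arm would be the willing ones, and willingness plausibly relates to diet, exercise and treatment adherence, all of which move HbA1c.

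The HbA1c threshold raises a second question, because it selects on the outcome variable. If it were applied to one arm only, the arms would differ at baseline, and regression to the mean could look like benefit. The primary result is the between-arm difference in HbA1c change over one year, so its causal reading depends on this step.

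**Working it through.** The point is procedural and no figure in the plan is at issue. The recruitment target used in the fix does reproduce: 60 / (1 − 0.20) = 75 per group, and 2 × 75 = 150.

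**Step 1: the sections side by side**

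| Question | What the protocol gives | Where |
|---|---|---|
| Pool sampled | Existing list of clinic patients | Methods for the randomization |
| What the draw produces | The intervention group | Same |
| Who is checked afterwards | The drawn group | Same |
| How controls arise | Not stated | No section |
| When consent is taken | Column after randomisation | Chronogram |
| First study laboratory tests | Column after randomisation | Chronogram |
| Criterion tied to one arm | Acceptance of peer education | Inclusion criteria |
| Blinding and custody | Open trial; list held by the principal researchers; no concealment described | Sample size section; Methods for the randomization |

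The Eligibility criteria section refers back to the randomisation section for how patients are chosen, so it gives no fuller procedure. The evidence on timing is the column order. The month labels cannot serve as dates, because T0, T3, T6 and T12 stand in consecutive Months 8 to 11.

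Followed literally, acceptance of education and agreement to the biological measures can be settled only after the draw. The same probably holds for HbA1c: no study test is scheduled earlier, and the routine consultation described under Comparison group lists blood glucose but not HbA1c. The protocol does not say which HbA1c value decides eligibility.

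**Step 2: a hypothetical for scale**

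Inputs: mean 8.5 and SD 2.0, which the sample size section gives for the reference group; threshold 8% from the Inclusion criteria. Assumptions not in the documents: these figures describe the unscreened list, HbA1c is normal with a stable mean and SD over time, only the intervention arm is screened, and the correlations are as shown.

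- Standardised threshold: (8 − 8.5) / 2.0 = −0.25.
- Share at or above 8%: 1 − Φ(−0.25) = 0.599. Of 75 drawn, 75 × 0.599 ≈ 45 stay and about 30 leave.
- Mean of those who stay: 8.5 + 2.0 × φ(0.25) / 0.599 = 8.5 + 2.0 × 0.387 / 0.599 ≈ 9.79. The gap to an unscreened arm is 1.29 points (0.9 to 1.7 for SD 1.5 to 2.5).
- If the screening value is the baseline, the spurious extra fall is (1 − r) × 1.29, where r is the correlation between the screening and one-year values:

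| r | 0.8 | 0.7 | 0.6 | 0.5 |
|---|---|---|---|---|
| Spurious fall (points) | 0.26 | 0.39 | 0.52 | 0.65 |

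- If a separate T0 value is the baseline, the spurious fall is (r between screening and T0 − r between screening and one year) × 1.29. With 0.8 for the first and 0.8 to 0.5 for the second, it runs from 0 to 0.3 × 1.29 = 0.39.

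The effect the trial is designed to detect is 1 point.

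**The case against.** The strongest reply is that the protocol means to run an ordinary randomised trial and that the randomisation section is just badly worded. The design is called randomised in three places. The criteria are presented as those of the study, not of one arm, and the section on risk minimisation requires consent from all subjects. The Chronogram also ticks identification of patients before the randomisation column as well as in it, so some selection may precede the draw. On this view controls are the undrawn patients, screened in the same way.

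Part of this stands. A reader might infer that only the intervention arm is screened, or that the two arms are simply not randomised. The documents do not support either as fact: the first is drawn from silence about controls, and the declared intent points the other way.

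The reply does not repair the procedure. None of those statements says how controls are formed or puts consent or eligibility before allocation. Even if undrawn patients were screened identically, exclusions and refusals would still follow a known allocation, and the acceptance criterion would still bear on one arm.

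The objection to the arithmetic also stands in large part. The 8.5 and 2.0 are given for the reference group, not for the clinic list. The range of 0.26 to 0.65 needs the screening value to be the baseline, whereas the primary criterion runs from inclusion and laboratory tests are ticked at both pre-inclusion and T0. The planned baseline comparison and multivariable models might expose or partly adjust for an HbA1c imbalance. They would not remove selection by willingness, and the methods section names no analysis population.

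**Conclusion.** The concern holds as a fault in the written procedure. Taken literally, the randomisation section, the Chronogram and the acceptance criterion together allow arm-dependent exclusions and refusals after allocation is known, in an open trial with no concealment described. They conflict with the randomised design declared in the abstract and the sample size section. This conclusion rests on the text and needs no numerical assumption.

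The size of the bias cannot be derived from the documents. The gap of about 1.3 points and the spurious falls computed above show only what one-sided screening could do under the stated assumptions. They are not estimates for this trial, and the regression component may be nil with a separate T0 baseline. Selection by willingness is not quantified at all.

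**What to change.** Rewrite Methods for the randomization and reorder the Chronogram columns so that the steps run as follows:

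1. Screen all candidates from the list against the same criteria, with HbA1c measured at pre-inclusion.
2. Obtain consent to assignment to either arm. This replaces acceptance of peer education as an inclusion criterion.
3. Randomise the 150 eligible, consenting patients 1:1, with the allocation concealed until each patient is enrolled.
4. Analyse all randomised patients in the arm assigned.

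State explicitly that both groups arise from this one step. Randomisation need not wait for T0, and blocking by diabetes unit is optional. If allocation has already taken place, document how controls were obtained and report by arm the numbers drawn, excluded and refusing.

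The cost is mainly wording and a reordered schedule, since pre-inclusion tests are already planned. Education groups form slightly later. Some more listed patients may need a pre-inclusion HbA1c test: on the hypothetical share of 0.599, finding 75 eligible controls means testing about 75 / 0.599 ≈ 125, or about 50 more than if controls were not screened.

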#### IV - Describe the supporting institutions

##### **National hospital Point G – endocrinology and diabetology unit – Bamako – Mali**

The hospital will realize the implementation and monitoring of the project in Mali in collaboration with the NGO Santé Diabète Mali (SDM). The strict collaboration between national hospital and University Hospital will permit to have support by the epidemiology department of the Faculty for the processing and data analysis

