## CALCULATION OF THE SIZE OF STUDY

In this trial, the patients were randomized into 2 groups:

- Group 1: group educational intervention by peer educators associated with classical management
- Group 2: classical management without peer education

This is a randomized trial comparing open impact on HbA1c of a 1 year peer education compared to a conventional monitoring alone in health centre.

The comparison group is on HbA1c, the primary judgement criteria. The test is a test of superiority. It is assumed that in the reference group, the value of HbA1c is 8.5% and with a **standard deviation of 2.0**, (previous study conducted in the framework of the NGO Santé Diabète Mali under publication) and we consider that the strategy would be interesting if the assessed value of the mean HbA1c decreased by 1 percentage point of HbA1c and the standard deviation of 0.5 .

In this situation, with a risk  $\alpha$  of 5% and a power  $1-\beta$  of 80%, we must include 60 patients in each group.

in order to take into account a proportion up to 20% of patients lost of sight, we decided to recruit 75 patients per group that is to say 150 patients in total.

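### Patients are drawn for the intervention arm before eligibility and consent, the principal researchers keep the list, and no allocation concealment is described

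*Supplement*

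**What the plan says.** Under Methods for the randomization, the starting point is a numbered list of patients attending the diabetes consultations of Bamako. From it, "a selection will be will randomly conducted with a number table to constitute the intervention group". The next sentence reads "We will verify that all the patients randomly selected to form this group meet the inclusion criteria of the group". The section ends with custody: "The randomization list will be kept by the principal researchers of the survey".

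The Chronogram gives its first columns in the order "Preparation | Randomization | Pre inclusion", followed by inclusion at T0. The row "Informed Consent" is ticked only under pre-inclusion. Clinical examination and laboratory tests are first ticked in that same column.

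The Inclusion criteria require, among other things, HbA1c of at least 8% and regular clinic attendance. They also list "Patients who accepted to undergo the whole process of peer education". The Non-inclusion criteria exclude irregular attenders, patients with recent severe complications, and patients with other illness serious enough to threaten function or life.

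The sample-size section describes the design in these words: "This is a randomized trial comparing open impact on HbA1c".

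**The concern.** Random selection protects comparability only if the people who decide whether a patient enters do not know, at that moment, which arm the patient would join. Here the draw names identifiable patients for the education arm before their eligibility and consent are settled, and the list stays with the research team. Nothing in the text keeps the arm from influencing those later decisions.

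The stake is the comparability of the two groups on the primary criterion, the change in HbA1c from inclusion to one year. Patients who attend regularly and are willing to sit through several education sessions may improve more than others under usual care too. If such patients are retained more readily in one arm, part of the observed difference would reflect who was enrolled and not the education. A laboratory endpoint limits bias in measurement, but not bias in who is measured.

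**Working it through.** No figure in the plan underlies this point, so the check sets the sections side by side and follows one patient through the steps as written.

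1. **Draw.** A patient on the numbered clinic list is selected with a number table for the intervention group (Methods for the randomization). The patient is identifiable and the arm is now fixed.
2. **Custody.** The principal researchers keep the list (same section). Under Risk minimization, the principal researcher, co-researchers and analysts also hold the keys linking study identifiers to personal data. That rule serves confidentiality and does not conceal allocation.
3. **Eligibility.** The check comes after the draw, and the sentence describing it mentions only those drawn for the intervention group. Some criteria are hard, such as age 30 to 70 and HbA1c of at least 8%. Others need judgement: what counts as regular attendance, as a severe complication, or as a threat to prognosis. One depends on cooperation with a single arm, namely acceptance of the peer education process.
4. **Consent.** The Chronogram has randomisation in month 6, pre-inclusion with consent in month 7 and inclusion in month 8. The month labels cannot all be literal, because T0 stands under month 8 and T12 under month 11. The order of the columns is nevertheless clear, and it agrees with step 3.
5. **Exclusion, refusal and replacement.** HbA1c is not among the items listed for classical management, and the first laboratory tests in the Chronogram are at pre-inclusion. Some drawn patients may therefore prove ineligible or decline. The plan does not say whether they are replaced, from where, or by whom, although it fixes 75 patients per group.
6. **Search for concealment.** No section mentions sealed envelopes, telephone or central allocation, an independent custodian, or a separation between list holder and recruiter.

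Steps 1 to 6 leave three decisions open to knowledge of the arm: whom to exclude, how consent is sought and given, and whom to bring in instead.

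**Size.** If the arms differed in the share of patients with a favourable outlook by p1 − p0, and those patients improved by δ more regardless of arm, the spurious difference would be (p1 − p0) × δ. The documents give none of these quantities, so no number can be put on it.

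**The case against.** Several counter-arguments have force.

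- **Who enrols.** A reader might infer that the keepers of the list also lead recruitment. The documents do not say so. The Method(s) paragraph has participants recruited through the local patients' association, the source list comes from the diabetes consultations, and health workers of the area are to be involved. The nearest support is the first person plural in the eligibility sentence. Keeping the list could also mean only storing it. This objection stands: shared roles are possible but not documented.
- **Foreseeing the next assignment.** A reader might picture investigators reading ahead and timing entries to obtain the arm they want. The text describes an up-front draw and not allocation one patient at a time, so there is no next assignment to foresee. What remains is selection after the draw.
- **Custody alone.** Giving the list to someone else would not cure the problem, because the written order still reveals the arm before eligibility and consent. This is right: the fault lies in custody together with the order of steps.
- **Open design.** Being open does not prevent concealment before enrolment, so it adds little to the case.
- **Analysis.** The baseline comparison and multivariable models under STATISTICAL METHODS USED can address part of an imbalance in measured variables. No measure of motivation appears among the judgement criteria, so the protection is partial.

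None of this supplies concealment or reverses the order of steps.

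**Conclusion.** The point holds in this form: the arm is drawn before eligibility and consent, the list is with the principal researchers, and no concealment is described. Followed as written, the plan lets knowledge of the arm affect exclusion, refusal and replacement. The documents do not show that anyone would use this knowledge deliberately. Differential screening can arise without intent.

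The size and direction of the bias cannot be estimated from the documents. The conclusion rests on reading the order in Methods for the randomization and in the Chronogram as the intended sequence; the two agree. It does not depend on who approaches patients. The change is worth making before enrolment because the models planned for the analysis can adjust only for what was measured.

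This point should be settled together with any correction to the timing of randomisation relative to eligibility and consent, since one repair serves both.

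**What to change.** Replace the custody sentence, and the draw that precedes it, with wording such as:

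> Consent, eligibility and the T0 HbA1c are recorded first. Each patient is then assigned 1:1 from a sequence with random blocks, generated and held by a person who has no role in enrolment. Assignments are released one patient at a time, by telephone or by sequentially numbered opaque sealed envelope. No investigator has access to the list.

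The Chronogram should be aligned so that randomisation follows pre-inclusion and the T0 measurements. The eligibility check should be stated to apply identically to all patients, before assignment, and a count of those screened, excluded and refusing should be kept.

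A possible custodian is at hand: the section on the National hospital Point G foresees "support by the epidemiology department of the Faculty for the processing and data analysis". Because that department may also handle the analysis, the custodian should preferably not be the trial analyst, and the absence of any enrolment role should be confirmed.

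**Cost.** The change needs a protocol amendment, a revised randomisation schedule, envelopes or a telephone line, and a short added step at each inclusion. Education groups of 8 to 10 would fill as patients are assigned. At 1:1 that takes about 16 to 20 inclusions per group (2 × 8 to 2 × 10), and the planned pace is 150 / 4 = 37.5 inclusions per month. The sample size of 75 per group is unaffected.

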### **Eligibility criteria**

The study will be conducted among patients with type 2 diabetes followed in the decentralized diabetes units of Bamako. The methodology used to choose patients is described in the paragraph above. The recruitment will last during four months.

### **Inclusion criteria**

- Patients followed in the diabetes units of the project area and doing regular consultations
- Patients with type 2 diabetes or treated or not with insulin
- Poorly controlled diabetes with HbA1c  $\geq 8\%$
- Patients who accepted to undergo the whole process of peer education
- Patients who agreed to perform all biological measures included in the protocol
- Patients aged from 30 to 70 years old

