**Method (s) :**

This study will be conducted by a multidisciplinary team that brings together high level skills in research projects and in peer education projects. It will be conducted in one site in one country Mali. This site was chosen because they meet a functional care, access to medicines and a dynamic association of diabetic patients. Peer educators and persons targeted by the project will be recruited through the local association of patients. This association will be a social support that provides on going prevention counseling, education and support services to people who have diabetes. It represents an important link between patients, educators and general medical services. The procedure will start by the training of peer educators who were identified and recruited to facilitate the sessions. Then, the 4 educational sessions: control of cardiovascular risk (blood pressure, waist circumference, smoking, cholesterol, glycaemia), control of Food (balance, fat, carbohydrates), physical activity management, insulin management, will be carried out and patients will be able to:

- Analyze knowledge that appears in various forms, including forms adapted to illiterate patients (colour codes, presence of photos)
- Act on knowledge: the patient observes, makes hypothesis, he experiments, compares, deduces, analyzes, makes relations.
- Work in interaction with other learners, which gives education a social dimension.
- Decide on the implementation of actions taking into account individual, cultural, social, economic context

For each situation, a day of training will be conducted by trained peer educators with theoretical contributions on the issue, practical scenarios, analyzes of the issues out of frame and put in "educational security ". These training days will be implemented with 8-10 patients (1Hour and an half) and the 4 sessions will take place over a period of two months starting from the inclusion of patients.

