During each education session, interactive workshops will allow to work on: a balanced diet, carbohydrates in the diet, cardiovascular risk and understanding of diabetes. For each situation, a one-day training will be conducted by trained peer educators with theoretical input on the issue dealt with, put in practice situation, analyses of issues outside the framework in "safety education". These training days will be implemented with patients (1H 30) and 3 meetings will take place over a period of 2 months. An educational replay will be made 6 months after, 12 after and 18 months after. The educational booklets will be available for patients at the end each meeting. It is important to that the tools used in this methodology allow for accessibility of learning by people with low literacy rates. It allows also the reproducibility of the education sessions because these sessions are designed and supervised, with brochures for patients, guides for teachers, and indicators of learning during the course.

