### **Main judgment criteria**

The main judgement criteria on which the analysis will be done to comply with the superiority of the contribution of a group educational approach by the peer will be the evolution of the HbA1c from the inclusion to 1 year:

- the HbA1C gives a reliable reflection of the glycemic control that is not subject to short-term variations or bias caused by the social aspects that may influence self-evaluation of data;
- it responds directly to all practices that peer education aims to change (diet and exercise, self glucose monitoring, proper use of drugs etc ...)
- It is the most important physiological parameter to improve for people with diabetes, as it is related to the probability of occurrence of micro-and macro vascular complications.

For the measurement of glycated hemoglobin, the apparatus used will be the machine "Infopia". The preservation of the reagent throughout the study will be precisely monitored to avoid, with high temperatures, deterioration of reagents and therefore invalid action. The reagents will be stored in reagents storage structures of the laboratories of the health facilities involved. The measures will be undertaken by the laboratory assistants of the structures involved in the project and who will have been beforehand trained.

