## STATISTICAL METHODS USED

The data will be analyzed by a medical epidemiologist with the Epi Info software.

Initially, we will proceed to the description of the included patients and compare the characteristics of both groups of patients to detect any differences at inclusion. These characteristics are expressed as percentage for qualitative variables and as mean and median and their dispersions parameters, respectively, standard deviation and interquartile 25 and 75. The comparison of characteristics between the two groups will be performed using appropriate tests, the exact X2 or Student's t-test. Then, a uni-variable analysis of variance analysis type will be conducted to identify variables to include in the multivariable explanatory models. The inclusion threshold chosen will be 0.25. Data will be expressed as means  $\pm$  SD unless indicated otherwise. Comparisons within groups were performed using analysis of variance by comparing the averages using the comparison test of averages or the Student's t-test.

The comparison between groups will be conducted by analysis of variance, using the Bonferroni correction where appropriate. The results will be statistically significant at  $p < 0.05$ .

**Direct beneficiaries in Mali:** The 150 diabetic patients directly reached by the activities / The 15 peer educators trained in the action areas selected in Mali. The 25 health agents of the action areas selected in Mali / Families and relatives of patients reached by animations (10 000 persons)

**Indirect beneficiaries in Mali :** All the diabetic patients of Mali (3% of the adult population) / All the health workers involved in the management of diabetes in Mali / The Malian health systems / The Malian population by reducing the risk factors of diabetes and increasing the quality of life

**Indirect beneficiaries in Africa:** Diabetic patients of French and English speaking African countries which will benefit from the methodology and tools developed

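### Insulin use has no pre-specified place in the between-group HbA1c comparison and can enter only through a p < 0.25 screen; the cost is modest precision and an unfixed adjusted estimate, not bias

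*Supplement*

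**What the plan says.** - **Eligibility** (Inclusion criteria): "Patients with type 2 diabetes or treated or not with insulin". Both kinds of patient enter. The expected share on insulin is not given.
- **Allocation** (Methods for the randomization): "From this numbered list, a selection will be will randomly conducted with a number table to constitute the intervention group". No stratification factor is named, and eligibility is checked after the draw.
- **Primary endpoint** (Main judgment criteria): "the evolution of the HbA1c from the inclusion to 1 year".
- **Analysis** (Statistical methods used): "The comparison between groups will be conducted by analysis of variance", with a Bonferroni correction where appropriate and no covariate named. The same section plans a comparison of the arms at inclusion, and multivariable explanatory models whose variables are chosen by univariable screening at a threshold of 0.25. It does not list the variables to be screened, and it does not say whether the analysis of variance or a multivariable model gives the primary result.

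**The concern.** Insulin use at inclusion is a simple yes/no factor that may well be related to how HbA1c moves over a year. A covariate fixed in advance reduces residual variance if it is prognostic and costs almost nothing if it is not. When covariates are instead selected on p-values from the trial's own data, the adjusted treatment estimate depends on which variables happen to pass. In an open trial with no designated primary model, that leaves a choice to be made after the data are seen. At stake are some precision and a primary estimate that could have been fixed beforehand.

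**Working it through.** **Inputs from the protocol** (Calculation of the size of study): target difference 1 point, SD 2.0 in the reference group, 5% alpha, 80% power, 60 evaluable and 75 recruited per group. Two-sided testing is assumed, because the protocol states only superiority.

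**Assumed inputs, not in the protocol:** share on insulin p = 20%, 30% or 50%; difference in mean HbA1c change between insulin users and others D = 0.5, 1.0 or 1.5 points. The SD of 2.0 is applied to the change, although the protocol attaches it to an HbA1c level of 8.5%.

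**Step 1: the plan's own figure.** n per group = 2 × (1.960 + 0.842)² × 2.0² / 1² = 62.8, so 63 rather than 60. At 60 per group the power is 78.2%; at 75 it is 86.5%. The allowance for loss reproduces: 60 / (1 − 0.20) = 75. The second SD of 0.5 is of unclear meaning. If it is the SD in the education arm, n = (1.960 + 0.842)² × (2.0² + 0.5²) = 33.4, so 34, and 60 per group gives 96.4% power. Little power would then be left to gain. The rest uses a common SD of 2.0.

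**Step 2: variance explained by insulin use.** R² = p(1 − p)D² / 2.0², and residual SD = 2.0 × √(1 − R²).

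| p | D | R² | Residual SD | n per group | Power at 60 |
|---|---|---|---|---|---|
| 20% | 0.5 | 1.0% | 1.990 | 63 | 78.6% |
| 20% | 1.0 | 4.0% | 1.960 | 61 | 79.8% |
| 20% | 1.5 | 9.0% | 1.908 | 58 | 81.9% |
| 30% | 0.5 | 1.3% | 1.987 | 62 | 78.7% |
| 30% | 1.0 | 5.3% | 1.947 | 60 | 80.3% |
| 30% | 1.5 | 11.8% | 1.878 | 56 | 83.1% |
| 50% | 0.5 | 1.6% | 1.984 | 62 | 78.8% |
| 50% | 1.0 | 6.3% | 1.936 | 59 | 80.7% |
| 50% | 1.5 | 14.1% | 1.854 | 54 | 84.0% |

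The gain at 60 per group is 0.4 to 5.8 power points. At 75 per group power goes from 86.5% to between 86.8% and 91.0%, a gain of 0.3 to 4.5 points.

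**Step 3: chance imbalance.** The SD of the difference in insulin share between arms is √(2p(1 − p)/n). At 75 per group, 1.96 times this is 13 to 16 percentage points. Multiplied by D, the shift in the HbA1c difference at that limit is 0.06 to 0.24 points, against a target of 1. At 60 per group the limit is 14 to 18 percentage points and the shift 0.07 to 0.27. This variation is already inside the standard error of an unadjusted comparison.

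**Step 4: would the screen pick insulin up?** Suppose insulin use is screened against HbA1c change in 120 evaluable patients. The SE of the gap is residual SD / √(120 p(1 − p)), and the two-sided critical value at 0.25 is 1.15. The chance of passing is about Φ(D/SE − 1.15) + Φ(−D/SE − 1.15).
- D = 1.0: p = 20% gives SE = 1.960/√19.2 = 0.447 and about 86%; p = 50% gives SE = 1.936/√30 = 0.353 and about 95%.
- D = 1.5: about 99% or more.
- D = 0.5: about 49% to 60%.

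**The case against.** The strongest reply is that the plan partly deals with this already. It compares the arms at inclusion and uses a liberal screen. If insulin use is among the screened variables, Step 4 shows that it would usually enter when the gap is 1 point or more, and would often be missed only at 0.5 points, where it matters little. That stands, and it limits the size of the point. What remains is that nothing guarantees insulin use is screened at all, and that neither the covariates nor the primary model is fixed in advance.

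It is also fair to say that the size rests on two assumed quantities, and that insulin is not the only candidate: baseline HbA1c has at least as strong a claim. Both stand.

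A reader might infer four stronger things, which the documents do not support:
- **That pooling the two kinds of patient is an error.** It is a legitimate pragmatic criterion.
- **That chance imbalance in insulin use biases the result.** Under random allocation it does not; the 5% error rate covers it.
- **That a quarter of the programme applies only to insulin users.** The Method(s) part of the abstract lists four sessions, including "physical activity management, insulin management, will be carried out". The Global method text in Details of application lists cycles on cardiovascular risk, food and physical activity, with no insulin cycle, and then states that "3 meetings will take place over a period of 2 months". Nowhere is a session restricted to insulin users. These descriptions must be reconciled, and the present point does not rest on either.
- **That the draw should simply be split by insulin status at inclusion.** Patients are drawn from the clinic list before eligibility is verified, and the Chronogram puts randomization in Month 6, pre-inclusion in Month 7 and inclusion in Month 8. No eligible list with that status exists when the draw is made.

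**Conclusion.** The point holds as a minor, nearly free improvement. The between-group HbA1c analysis has no pre-specified insulin term, and insulin use can enter a model only through data-driven selection. The consequence is a modest loss of precision and an adjusted estimate that is not fixed in advance. Power at 60 per group would rise by about 0.4 to 6 points (1% to 14% of variance removed) if 20% to 50% of patients use insulin, the gap in HbA1c change is 0.5 to 1.5 points and the common SD is 2.0. For a 1-point gap, the required number falls from 63 to 59 to 61 per group, about the planned 60. These figures treat insulin as the only covariate; its added value once baseline HbA1c is in the model cannot be derived from the documents. The statement that there is no bias presumes that allocation is otherwise properly random.

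**What to change.** In Statistical methods used, designate one primary model for HbA1c change from inclusion to 1 year. Give it fixed terms for group, baseline HbA1c and insulin use at inclusion (yes/no), and do not leave these terms to the 0.25 screen. Because inclusion follows the draw in the Chronogram, state that insulin use is recorded before the first education session. Report the effect estimate with its confidence interval by insulin status as description only, without a subgroup test.

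The insulin term costs one degree of freedom out of roughly 120 evaluable patients, with no extra patients or visits. Stratifying the draw is worth considering only if insulin status is already recorded on the clinic list when the draw is made; otherwise the order of eligibility check, consent and randomization would have to change.
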